## Abstract

**Background:**

In recent decades, several studies have assessed the value of cardiac rehabilitation as secondary prevention and have reported substantial reductions in readmissions. However, conclusive evidence is scarce. The present study aims to evaluate the efficacy of a supervised exercise training program for improving percentages of hospital readmission for cardiac causes in patients with myocardial ischemia in the first year after a cardiac event. The effect on all-cause readmission, all-cause mortality, functional capacity, quality of life and adherence to regular exercise is also discussed.

**Methods/Design:**

This study will be conducted as a randomized controlled trial. Eligible patients will be randomly assigned to a control group receiving standard care or to an intervention group which, in addition to standard care, will take part in a supervised exercise training program consisting of three hours a week (spread over three alternate days) of supervised exercise training for 10 weeks. Both groups will perform an exercise stress test and a blood test during the first and third month after hospital discharge. The follow-up period will be 12 months after hospital discharge. The primary outcome measures will be the percentage of patients readmitted, total number of readmissions and length of hospitalization for cardiac disease during the first year after hospital discharge, and time to first hospital admission for cardiac disease.

**Discussion:**

A representative group of hospitalized patients after myocardial ischemia will be studied in order to provide comprehensive data on the potential impact of a supervised exercise training program on hospital readmission rates.

**Trial registration:**

Current Controlled Trials ISRCTN57634424.

## Background

Cardiovascular disease (CVD) is a first-order public health problem all over the world. In 2005, 17.5 million CVD-associated deaths were recorded, and the World Health Statistics 2008 report [1] predicts that this figure will rise to 23.4 million by 2030. In Europe, CVD is the main cause of mortality and has a major impact on health care costs. In Spain, CVD accounts for 35% of all deaths and also has a high morbidity. It is particularly important as a cause of death from age 65 onwards.

Improved diagnosis and more successful treatment of acute illness have increased survival rates after myocardial ischemia (MI). However this also means that the prevalence of CVD is increasing.

In 1964, the World Health Organization (WHO) [2] defined cardiac rehabilitation as "the sum of activity required to ensure cardiac patients the best possible physical, mental, and social conditions so that they may, by their own efforts, regain as normal as possible a place in the community and lead an active life." Since then, several institutions have introduced cardiac rehabilitation in order to offer an integrated physical, psychological and social approach to the treatment of the cardiac patient. In cooperation with the American Association of Cardiovascular and Pulmonary Rehabilitation (AACVPR), the American Heart Association (AHA) published recommendations for cardiac rehabilitation programs (CRP) [3], specifying that these programs should include physical training, aggressive treatment of cardiovascular risk factors, dietary guidance, psychosocial, occupational and physical activity, and the use of all cardioprotective drugs with proven efficacy in secondary prevention. In addition to these recommendations, and where possible, CRPs should include appropriate secondary prevention measures as part of a comprehensive multifactorial approach and should apply the standards of European societies [4]. Secondary prevention through exercise-based cardiac rehabilitation is the approach that has been most successful in reducing morbidity and mortality in coronary artery disease, particularly after MI; CRPs are recommended (Class I), by the European Society of Cardiology, the American Heart Association and the American College of Cardiology [5]. Secondary prevention and cardiac rehabilitation form a single strategy for CRPs designed to reduce heart disease-related morbidity and mortality and the disability it causes by 20-30% [6].

Despite the acknowledged benefits, however, CRPs are currently underused. According to the European Cardiac Rehabilitation Inventory Survey (2008)[7,8], of the 47.5% of the countries that answered the survey, 42.10% (including Belgium, Spain, and Italy) admitted ≤ 30% of eligible patients for phase II of CRP; 15.79% (Luxembourg, Sweden, UK) admitted >30-50% of eligible patients, and 15.79% (Germany, Iceland, Lithuania) admitted >50%. Data were unavailable for the remaining 26%.

Studies on post-MI survival, readmissions and physical rehabilitation date back to 1972 [9]. Most studies have found no significant differences in readmissions post-CRP but in 2005 one study concluded that global community CRP significantly reduced cardiac readmission rates [10]. In 2011, Heran et al. [11] published an updated systematic review of Jolliffe et al’s 2001 study, finding that exercise-based CRPs significantly reduced hospital admissions in the short term (<12 months), and in the same year Lawler [12] published the first meta-analysis showing a statistically significant reduction in MI recurrence with an exercise-based CRP post-MI (OR 0.53; 95% CI: 0.38 - 0.76). Moreover, the few studies of the issue do not focus on identifying the best exercise regimen for reducing readmissions, but on whether the intervention itself affects readmission rates. Only two of the studies presented statistically significant decreases in readmissions [10,12]. The value of readmission as an indicator of effectiveness of exercise lies in the fact that it is an indirect measure of clinical stability, so there is a clear need to study the relation between CRPs and readmission in MI patients.

The aim of this study is to evaluate the efficacy of a supervised exercise training program for reducing cardiac readmissions in patients with MI in the first year after hospital discharge. This study will also provide a detailed evaluation of the program’s effects on total mortality, functional capacity, quality of life and adherence to regular exercise. Our primary hypothesis is that a supervised exercise training program will significantly reduce the incidence of cardiac readmissions in patients with MI in the first year after hospital discharge. The secondary hypothesis is that patients in the intervention group will present significantly better functional capacity, better quality of life, and lower mortality rate.

## Methods/design

### Study design

Open, controlled, randomized, hospital-based clinical trial of patients admitted to the Cardiology Department for MI.

### Study subjects and recruitment

The study will recruit adult patients discharged from hospital with MI as a primary diagnosis. Inpatients will be actively identified by the cardiac nurse and the CRP physiotherapist using daily bed lists.

The inclusion criteria will be: age over 18, diagnosis of MI (myocardial ischemia, pre-infarct angina, cardiac angina, other specific forms of chronic ischemic heart disease or unspecified ischemic heart disease) in the current admission, residence in the catchment area of our hospital, absence of cognitive deficit (Pfeiffer test: 0–2 mistakes), sufficient autonomy to follow the cardiac rehabilitation program (Barthel index >60), and willingness to participate in the study. Signed informed consent will be obtained in all cases. Patients will be excluded if they have symptoms of right heart failure producing pulmonary hypertension or dyspnea caused by severe pulmonary pathology, additional comorbidities affecting the prognosis of cardiac disease, major comorbidities or limitations that could interfere with exercise training program, cognitive impairment or if they do not provide informed consent.

### Randomization

Patients will be randomly assigned to one of two groups: control or intervention. Patients in the intervention group will be included in the supervised exercise training program, while controls will receive standard care. A randomization list will be produced by a computer-generated random-number sequence in blocks of 10 to ensure consistent patient distribution in both groups. The randomization list will be generated by the Clinical Research Unit, which will also control allocation to each group. The researchers will not be aware of the randomization scheme.

Patients will be recruited by the cardiac nurse and the CRP physiotherapist. Neither of them will know the group assignment until the patient has signed the informed consent form. The cardiac nurse or the physiotherapist will then give the name and the patient identification number to the Clinical Research Unit by telephone. After this, participants in both groups will be scheduled for their first visit with the cardiac nurse and for the exercise stress test.

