### Data collection and measures

#### Procedure

Each day, the cardiac nurse and the physiotherapist will check the bed list of patients admitted to the Cardiology Department. They will select the eligible patients after assessing the clinical history and consulting the cardiologist. In the inpatient setting, the cardiac nurse or the physiotherapist will give verbal and written information related to the study to eligible patients and will resolve all the patients’ doubts. These professionals will stress to the patient that the randomization process will decide the group inclusion. Before discharge (visit −1), eligible patients who agree to participate will be asked to give signed informed consent. In this visit, the cardiac nurse will record the following variables: education level, marital status, living situation, employment status and comorbidities (Charlson Comorbidity Index). On discharge (visit 0) the cardiac nurse or the physiotherapist will contact the Clinical Research Unit regarding the randomization process. Once the cardiac nurse or the physiotherapist knows the randomization group, they schedule the patient for the first cardiac nurse visit and for the exercise stress test.

Patients will attend four cardiac nurse visits (visits 1, 2, 3 and 4). During these visits, the cardiac nurse will describe ways of improving cardiovascular risk factors and cardiac medication adherence, and will answer the patients’ questions. The following variables will be recorded: attendance, systolic blood pressure (SBP), diastolic blood pressure (DBP), heart rate, Body Mass Index (BMI), abdominal circumference, Mediterranean diet, depressive symptoms (Yesavage Geriatric Depression Scale), basic activities of daily living (Barthel index), tobacco dependence (Fargeström test), compliance with cardiac medication (Haynes-Sackett test), taking sublingual nitroglycerin, hospital emergency visits, hospital readmissions and mortality. Quality of life (EuroQol5) will be recorded at all visits except visit 3. To address a possible cross-over effect, all patients will be asked to complete a physical activity questionnaire (Capersen and Powell classification) at baseline and in each follow-up visit. This test categorizes physical activity in four levels: sedentary, irregular activity, non-intensive regular activity, and intensive regular activity.

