### Statistical issues

#### Sample size

To ensure a statistical power of 80% in order to detect differences in the contrast of the null hypothesis (H_0_: equal percentages of cardiac readmissions in the two groups) through a two-tailed chi-square test for two independent samples, with a level of significance of 0.05, and assuming that the percentage of cardiac readmissions in the control group is 25% and the percentage in the intervention group is 12%, each group will require 139 patients. Assuming a 5% loss to follow-up, we estimate that 146 patients will be needed in each arm.

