## Limitations

One limitation of this study is its open design, since it will not be possible to blind the intervention and both patients and staff will know to which group they have been assigned. This may affect the degree of response, especially in the control group. Another limitation may be the difficulty of including patients due to the large size of the catchment area and its mainly rural nature. This may restrict the inclusion process due to the distance and transport problems, and may limit the external validity.

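### The protocol says the randomization scheme is withheld, yet prints a constant block size of 10 in an open, single-hospital trial; this is an avoidable risk to allocation concealment

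*Protocol article*

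**What the plan says.** The Randomization section of the protocol article describes one list: "A randomization list will be produced by a computer-generated random-number sequence in blocks of 10". It gives a single block length and mentions no stratification. A separate Clinical Research Unit makes the list and controls allocation, and the section adds that the researchers will be kept unaware of the scheme.

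On who recruits, the same section says "Patients will be recruited by the cardiac nurse and the CRP physiotherapist". These two roles are not told the group until consent is signed, and they then telephone the unit. The Procedure section gives the same two roles the screening: "They will select the eligible patients after assessing the clinical history and consulting the cardiologist". Consent is taken before discharge (visit −1) and the call is made on discharge (visit 0). "Once the cardiac nurse or the physiotherapist knows the randomization group", the patient is booked for the first nurse visit and the stress test.

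The Limitations section confirms that "both patients and staff will know to which group they have been assigned". The trial runs at one hospital; eligibility requires "residence in the catchment area of our hospital". The Sample size section sets the total: "we estimate that 146 patients will be needed in each arm".

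**The concern.** Central telephone allocation hides the list. It does not hide what can be worked out from earlier allocations. In a permuted block of known length, whoever has seen the earlier assignments knows the remaining ones as soon as one arm's places are used up.

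The conditions that make this matter are present: an open trial, one unstratified sequence, and the same two roles screening, consenting, telephoning and then learning every result. Two exclusions rest on judgement: comorbidities affecting cardiac prognosis, and comorbidities or limitations that could interfere with training. The second bears directly on what only one arm is asked to do. A physiotherapist also supervises the training sessions, so a recruiting role has a practical interest in who is assigned to them.

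The section also pulls against itself: it says the scheme is withheld but prints the scheme's key parameter. At stake is the comparability of the arms. A foreseen assignment could affect whether a patient is approached, whether eligibility is reconsidered between consent and discharge, or which of two consented patients is telephoned in first.

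**Working it through.** **Inputs.** Block size 10, taken as 5:5 because the arms are equal (Randomization; Sample size). Total 2 × 146 = 292, that is 29 full blocks plus 2 patients. Assumed, not stated in the protocol: an observer who knows the block size and has a complete tally of past allocations.

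**The plan's own figure.** It is needed only for the number of blocks. With 25% against 12%, pooled proportion 0.185, two-sided 0.05 and 80% power:

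n = [1.96·√(2·0.185·0.815) + 0.8416·√(0.25·0.75 + 0.12·0.88)]² / 0.13² = (1.0763 + 0.4556)² / 0.0169 ≈ 138.9, so 139 per group, as stated. 139 × 1.05 = 145.95 gives the stated 146. (Dividing by 0.95 would give 147, which makes no difference here.)

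**Allocations certain in advance, fixed blocks of 10.** The last k are certain when all k belong to one arm, with probability 2·C(10−k,5)/C(10,5):

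- k = 1: 2·126/252 = 1.000
- k = 2: 2·56/252 = 0.444
- k = 3: 2·21/252 = 0.167
- k = 4: 2·6/252 = 0.048
- k = 5: 2·1/252 = 0.008

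The sum is 1.667 per block, which matches 2b/(b+1) = 10/6 with b = 5. The share is 1/6 = 16.7%. Over 29 full blocks it is 29 × 1.667 = 48.3; the two leftover patients add none. About 48 of 292 are therefore certain.

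**Best guessing.** Expected correct share = [b + (2^(2b)/C(2b,b) − 1)/2]/(2b) = [5 + (1024/252 − 1)/2]/10 = 65.3%, against 50% by chance.

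**Shorter fixed blocks are worse.** By 1/(b+1), blocks of 4 give 33% certain and blocks of 6 give 25%.

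**Varying block sizes.** Simulation over 292 patients, with an observer who knows the set of sizes but not the size of each block:

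| Block sizes | Certain | Best guess correct |
|---|---|---|
| 10 (fixed) | 16.6% | 65% |
| 6, 8, 10 | about 1.5–1.7% | 66% |
| 8, 10, 12 | about 1.2% | 65% |
| 6, 8, 10, 12, 14 | about 0.5% | 65% |

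Varying the sizes removes nearly all of the certainty. It does not improve the best-guess rate.

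**What it could do to the result (illustration; the risk gap is an assumption).** Suppose patients placed in certain slots differ in readmission risk by d according to the foreseen arm. One sixth of each arm is affected on average, so the group difference shifts by d/6: 1.7 points for d = 10 and 3.3 points for d = 20, against the planned 13 (25% − 12%). With no true effect, 25% in both arms and 146 per arm, the standard error is √(2·0.25·0.75/146) = 5.07 points. The shifts are then 0.33 and 0.66 standard errors, and two-sided type I error becomes roughly 6% and 10% instead of 5%.

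**The case against.** The strongest reply is that the protocol denies the premise. It says the scheme is withheld, a separate unit holds the list, and disclosure follows signed consent. A reader might infer from the printed block size that the recruiters can in fact predict assignments. The document does not support that: it is a journal article, and nothing in it shows whether the nurse or physiotherapist had this text, or otherwise knew the block length, while recruiting. This stands, so the point is conditional.

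Timing also helps the plan. Consent comes before discharge and the call comes at discharge, so allocation order follows discharge order, and a recruiter approaching an inpatient cannot be sure which slot that patient will take. This weakens the mechanism at the moment of approach. It leaves the interval between consent and the call, and the order of calls.

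Discretion over eligibility should not be overstated either. The autonomy criterion might look like a judgement call, but it is anchored by a Barthel index above 60, cognition has a Pfeiffer cut-off, and the cardiologist is consulted. Discretion lies in the comorbidity and limitation exclusions.

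A reader might also infer that no analysis could help. The planned adjusted Cox model could partly correct imbalance in measured prognostic factors, but not selection on characteristics that are not recorded.

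Finally, ten is a fairly large block. Even for a fully informed observer, five in six allocations are not certain.

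**Conclusion.** The point holds as a limited and avoidable weakness in allocation concealment, not as evidence of bias. The section should not claim that the scheme is withheld while publishing a constant block size. The size is about 1 in 6 allocations certain in advance (1.67 per block, about 48 of 292). That is an upper figure: it assumes recruiters know or infer the block size and that the two of them together keep a full tally. Without that knowledge, certainty is not available in the same way. The shifts of 1.7 to 3.3 points rest on a further assumption about patient selection and are only illustrative. Sample size and planned analysis are unaffected.

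**What to change.** Have the Clinical Research Unit generate the list, or its unused part if recruitment has begun, with randomly varying block sizes, for example a mix from 6 to 14. Withhold the sizes from the nurse and physiotherapist, and from any document they can see, until recruitment closes. In the Randomization section, state only that block sizes vary. Simply shortening the fixed block would make matters worse.

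The cost is regenerating the list. The downside is a possible small imbalance in numbers at the end of the trial, with negligible effect on power. The gain is in certainty, which falls from 16.7% to about 0.5–2%, and should be described that way, because best-guess accuracy stays near 65%.

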### Study arms

#### Control

Patients assigned to the control group will receive the standard care given at our hospital. During hospitalization, the cardiac nurse or the physiotherapist will assess the cardiovascular risk factors and other clinical variables in each patient. This assessment will check diet, tobacco consumption, hypertension, diabetes, exercise practice, family heart disease, dyspnea, depressive symptoms and activities of daily living. Patients will receive verbal and written information on cardiovascular risk factors from the cardiac nurse or the physiotherapist. This educational information will be related to cardiac disease, cardiovascular risk factors (hypertension, diabetes, cholesterol, triglycerides, tobacco and other drugs, alcohol, stress, overweight, sedentary lifestyle), lifestyle (progressive rehabilitation activities, return to work, driving), diet, physical exercise (phases of readaptation, phases of normal activity, work activity, sexual activity), specific medication in case of cardiac angina (nitroglycerin), pharmacological regimen, complementary assessment (electrocardiogram, echocardiogram, chest X-ray, SPECT, cardiac catheterization, arteriography, electrophysiological study) and treatment of coronary artery disease (pharmacological, coronary angioplasty, surgical treatment). Hospitalized patients will be instructed to do exercises to regain mobility in order to maintain and improve muscular tone and peripheral circulation, and will be taught breathing exercises by the physiotherapist to improve their breathing patterns. Before discharge, the physiotherapist will instruct patients on how to return to physical activity.

#### Intervention

In addition to the usual hospital care, patients randomized to the intervention group will be provided with a supervised outpatient exercise training program, according to the results of the exercise stress test performed one month after hospital discharge and bearing in mind the physical limitations imposed by co-morbid conditions. The program will be performed in the hospital and it will start within the three days after the exercise stress test. It will comprise three hours a week (spread over three alternate days) of supervised exercise training for 10 weeks. The intervention will end after 10 weeks, regardless of whether the patients have completed 30 sessions. Exercise classes will be supervised by a physiotherapist and will consist of 10 minutes of warm-up and muscle stretching, 30 minutes of aerobic exercises (cycloergometer), 15 minutes of isotonic exercises for the upper and lower extremities and 5 minutes of cool-down. Moreover, instructions will be given on self-pulse counting, subjective perception of effort using the Borg scale, relaxation exercises, breathing techniques, postural health and minimizing physical effort. Aerobic exercise intensity will be between 75-90% of the maximum heart rate obtained in the previous exercise stress test and progressing according to the rating of perceived exertion (RPE: Borg scale 11–15). Resistance training will be performed with 10–15 repetitions for three sets, maintaining an RPE of 11–14. The physiotherapist will check that patients are exercising at their prescribed intensity with a pulse oximeter (Quirumed® Health & Care).

After hospital discharge, patients in both groups will have scheduled follow-up visits with a cardiac nurse at the first month, and then after 3, 6 and 12 months (visits 1, 2, 3 and 4 respectively) since hospital discharge in order to control the risk factors, reinforce education for disease control and review adherence to cardiac medication and CRP follow-up.

Control patients will be asked to complete the same outcome measures as the intervention group (See Figure 1).

